# Therapy de‐escalation for testicular cancer (THERATEST): A multi‐centre observational cohort feasibility study of de‐escalation therapies for good prognosis stage II germ cell tumours

**DOI:** 10.1002/bco2.70057

**Published:** 2025-07-29

**Keywords:** carboplatin AUC10, De‐escalation therapy, feasibility study, pragmatic study, rRPLND, stage II seminoma

## Abstract

**Background:**

Standard of care (SOC) treatments for International Germ Cell Cancer Collaborative Group (IGCCCG) good prognosis stage II germ cell tumours (GCT) involve primary orchidectomy followed by combination chemotherapy for both seminoma and non‐seminomatous germ cell tumours (NSGCT). Alternatively, external beam radiotherapy may be used for seminoma and retroperitoneal lymph node dissection (RPLND) for NSGCT. While these treatments achieve high cure rates, they are associated with significant toxicities. De‐escalation strategies including three cycles of Carboplatin AUC10 or robotic RPLND with or without adjuvant chemotherapy have demonstrated potential to reduce treatment‐related toxicity in stage II seminoma while preserving oncological efficacy. However, these approaches are not widely adopted due to limited prospective comparative trials.

**Study Design:**

The THERATEST trial is a prospective multicentre observational feasibility study evaluating participants receiving SOC treatments for good prognosis stage II seminoma and NSGCT or de‐escalated treatments for stage II seminoma.

**Endpoints:**

The primary endpoints are to assess feasibility of recruitment and retention. Secondary endpoints include assessing health‐related quality of life (HRQOL), sexual function and satisfaction, progression‐free survival (PFS), overall survival (OS) and safety and treatment‐related complications.

**Patients and Methods:**

Thirty participants with good prognosis stage II seminoma or NSGCTs will be recruited over 18 months into two cohorts: de‐escalation arm and SOC arm. The de‐escalation cohort will receive either Carboplatin AUC10 or robotic RPLND with or without adjuvant therapy depending on institutional SOC. Participants who decline or are ineligible for de‐escalation will receive SOC treatment: combination chemotherapy or radiotherapy for seminoma and combination chemotherapy for NSGCT. All participants will be followed for two years post‐treatment or until withdrawal. Data collection includes recruitment and retention rates, disease status, surgical outcomes, adverse events and patient‐reported outcomes using validated questionnaire: EORTC QLQ‐TC26, EORTC QLQ‐C30, Brief Male Sexual Function Inventory (BMSFI) and additional enquiries on anejaculation.

**Trial registration number:**

ISRCTN61007118.

## BACKGROUND

1

Standard of care (SOC) treatments for International Germ Cell Cancer Collaborative Group (IGCCCG) good prognosis metastatic testicular germ cell tumours (TGCT) include primary orchidectomy followed by combination chemotherapy (three cycles of Bleomycin, Etoposide and Cisplatin (BEP) or four cycles of Etoposide and Cisplatin (EP))^1^ with cure rates exceeding 95%.^2^ Alternatives are external beam radiotherapy (30–36 Gy in 2Gy fractions) for stage IIA/B seminoma, and primary retroperitoneal lymph node dissection (RPLND) for selected marker‐negative stage IIA/IIB non‐seminomatous germ cell tumour (NSGCT). However, combination chemotherapy is associated with early haematological and non‐haematological toxicities (reviewed in^3^) and radiotherapy can lead to late effects, including second malignancies, resulting in reduced utilisation in some centres.^4^ RPLND is typically an open surgical procedure with associated morbidity, and key long‐term side effect is ejaculatory dysfunction due to surgical damage to the lumbar sympathetic chain and pre‐aortic plexus.

Within the good prognosis group, stage II seminoma shows the most favourable oncological outcomes with long‐term cure rates of exceeding 98%,^3^ leading to explorations of non‐SOC therapy de‐escalation to reduce treatment‐related toxicity and maintain oncological outcomes.^3^ A prospective multicentre study of a single cycle of neoadjuvant Carboplatin AUC7 with reduced field and dose of radiotherapy for stage IIA/B seminoma yielded 3‐year progression‐free survival (PFS) rate of 93.7% with minimal toxicity.^5^ In a multi‐centre cohort, three cycles of Carboplatin AUC10 monotherapy for stage II seminoma yielded a 2‐year PFS rate of 96.5% and a 3‐year cancer‐specific survival (CSS) rate of 100%^6^ with only myelosuppression being a major acute toxicity. A recent prospective clinical trial of RPLND without adjuvant chemotherapy in stage IIA/B seminoma showed a 31% recurrence rate over a mean of 26 months follow‐up.^7^ Another prospective trial of RPLND reported an 81% 2‐year recurrence free survival (RFS) and low toxicity in small volume stage IIA/B disease.^8^ Similarly, a prospective trial of nerve‐sparing RPLND for stage IIA/B seminoma showed a 10% recurrence rate at up to 9 months follow‐up.^9^ To reduce the recurrence risk, one group has adopted a single cycle of adjuvant Carboplatin AUC7 after minimally‐invasive robot‐assisted RPLND (rRPLND), which appears to have low toxicity and relapse rates.^10^

Despite high PFS rates, fewer toxicities and better quality of life outcomes, de‐escalated treatments are not yet widely adopted as SOC primarily due to a lack of comparative outcomes data derived from prospective randomised clinical trials and limited adoption of minimally invasive RPLND. Consequently, a recent UK survey highlighted significant geographical heterogeneity in SOC treatments for stage II seminoma, and only a third of centres have adopted a treatment de‐escalation regimen.^11^ TGCTs are a rare cancer and account for only approximately 1% of newly diagnosed malignant tumours,^12^ hence there are challenges in recruitment to randomised controlled trials (RCTs), including ethical concerns over randomisation without clear equipoise, and patient and clinician biases regarding SOC and de‐escalated options.

THERApy de‐escalation in TESTicular cancer (THERATEST) is a multi‐centre observational cohort feasibility study of patients receiving guideline‐recommended SOC treatments for good prognosis stage II seminoma (combination chemotherapy or radiotherapy) and NSGCT (combination chemotherapy) or novel de‐escalated treatments (primary rRPLND or Carboplatin AUC10) for stage II seminoma. In view of the rarity of testicular cancer, THERATEST adopts a pragmatic cohort design aimed at maximising participants' recruitment and reducing attrition, while aligning treatment strategies with institutional SOC. The study findings will inform the design and conduct of a future definitive trial, which may adopt a pragmatic cohort‐embedded design, by providing prospectively‐collected information on the safety and complications of treatments as well as health‐related quality of life (HRQOL) outcomes.

## STUDY DESIGN

2

The THERATEST trial is a multicentre observational feasibility of two cohort study. It includes patients receiving SOC treatments for good prognosis stage II seminoma (combination chemotherapy or radiotherapy) and NSGCT (combination chemotherapy) or de‐escalated treatments (primary rRPLND or Carboplatin AUC10) for stage II seminoma. If participants are not eligible for either of these de‐escalation strategies or decline treatment, they will be offered either combination chemotherapy or radiotherapy but remain within the study. In both cohorts, participants will be followed up for 2 years after treatment completion. Beyond the study period, participants will be followed up as per institutional SOC protocols as part of prospective institutional audits.

### Study settings

2.1

Three recruiting sites are planned with additional sites being added via a future protocol amendment. Participants will be recruited from within the National Health Service (NHS).

### Recruitment

2.2

Thirty evaluable participants with histologically confirmed good prognosis stage II seminoma and NSGCT who have not previously received chemotherapy or radiotherapy will be enrolled from UK sites. A minimum of 5 participants will be recruited into each treatment de‐escalation group within each cohort, and a maximum of 15 patients will be recruited into the SOC groups. In the event of withdrawal, participants will not be replaced in this feasibility study. Participants will be identified in the secondary care setting via supra‐regional multi‐disciplinary team (MDT) meetings at research sites.

## END POINTS

3

### Primary objective and endpoint

3.1

The primary objective of this study is to assess the feasibility of recruitment and retention by measuring the number of participants recruited per month and retained annually. The primary endpoint for this study is the successful recruitment of 30 participants into the THERATEST study within 18 months from the first participant enrolled.

### Secondary objectives and endpoints

3.2

1Health‐Related Quality of Life (HRQOL)
2Sexual Drive, Function and Satisfaction
3Progression‐Free Survival (PFS) and Overall Survival (OS)
PFS at 2 years is defined as the proportion of participants who do not experience disease progression or death from any cause within the 2‐year follow up period.OS at 2 years is defined as the proportion of participants who remain alive from any cause at the 2‐year follow up period.The study aims for these survival rates to remain consistent with SOC treatments (>95%).4. Safety and Treatment‐Related Complications
4Safety and Treatment‐Related Complications
The incidence, nature and severity of adverse events (AEs) will be documented according to the Common Terminology Criteria for Adverse Events (CTCAE) v5.0, from the time of informed consent until 6 weeks post‐surgery or 6 months post‐chemotherapy.Surgical complications will be classified using the Clavien‐Dindo scoring system, and additional safety assessments will include analysis of blood transfusion rates, ITU (Intensive Therapy Unit) admissions and dialysis requirements from patient records up to 6 months post‐rRPLND.

The study aims to evaluate changes in HRQOL before and after treatment(s). This will be assessed by measuring changes in domain scale scores and single‐item scores from the European Organisation for Research and Treatment of Cancer (EORTC) QLQ‐TC26 and EORTC QLQ‐C30 from baseline until the 2‐year follow up visit. 2. Sexual Drive, Function and Satisfaction

Another objective is to assess changes in sexual drive, function and overall satisfaction before and after treatment(s). This will be evaluated by tracking changes in domain scale scores and single‐item scores in the Brief Male Sexual Function Inventory (BMSFI), QLQ‐TC26 and supplementary anejaculation‐related questions, with assessments conducted from baseline to the 2‐year follow‐up visit.3. Progression‐Free Survival (PFS) and Overall Survival (OS)

The study also aims to evaluate PFS and OS rates to ensure they align with standard‐of‐care treatment outcomes.

The study seeks to assess the safety and complications associated with all treatments.

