#### Institutional standard of care treatments

5.1.1

*rRPLND*: Participants undergoing rRPLND will have robot‐assisted laparoscopic surgery to remove ipsilateral retroperitoneal lymph nodes(s) as per local Trust procedures. For participants undergoing rRPLND, adjuvant treatment decisions are based on post‐operative histology and is left to the shared decision‐making between treating clinician and participants as per local SOC. The adjuvant treatments typically used following rRPLND are summarised in Table 1. Data will be collected on the type of adjuvant treatment delivered.

**TABLE 1 bco270057-tbl-0001:** Typically‐used adjuvant treatments following rRPLND.

Post‐operative nodal histology	Adjuvant treatment
pN0 or pN1 teratoma only	No adjuvant treatment
pN1 mixed/NSGCT	1x Bleomycin, etoposide and platinum (BEP), OR 2x Etoposide and cisplatin (EP)
pN1 seminoma	1x Carboplatin AUC7 or 10
pN1 positive surgical margins	2x BEP, OR 2x EP (NSGST), OR 2x Carboplatin AUC10 (Seminoma)

*Carboplatin AUC10*: Carboplatin AUC10 is typically given intravenously once every 21 days for 3 cycles (as per local Trust procedures).

*BEP/EP*: BEP is given intravenously every 21 days over 3 cycles while EP is given intravenously every 21 days over 4 cycles (as per local Trust procedures).

*Radiotherapy:* Radiotherapy is delivered with 30Gy in 15 fractions to para‐aortic nodes and 5Gy in 3 fractions to ipsilateral iliac nodes. Alternatively, a single cycle of Carboplatin (AUC7) is followed by 30Gy in 15 fractions to para‐aortic nodes (as per local Trust procedures).

All agents listed above are non‐investigational medicinal products licensed in the UK for treatment of TGCT. Information regarding anti‐cancer treatments will be collected for all participants throughout the follow‐up period.

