### Study timeline

5.3

The tables below describe the participant timeline through the trial. Participants will attend visits according to the schedule outlined in Table 2 for the rRPLND cohort and Table 3 for the Carboplatin AUC10 cohort. These visits will include screening, treatment and follow‐up assessments to monitor progress and outcomes.

**TABLE 2 bco270057-tbl-0002:** Schedule of assessments for rRPLND cohort.

	Screening	rRPLND	2 weeks	6 weeks	12 weeks	6 months	9 months	12 months	15 months	18 months	21 months	24 months	Disease recurrence
	<6 weeks pre‐surgery		± 2 weeks	± 2 weeks	± 2 weeks	± 2 weeks	± 2 weeks	± 4 weeks	± 4 weeks	± 4 weeks	± 4 weeks	± 4 weeks	+4 weeks
**Informed consent**	X												
**Demographic data & medical history**	X												
**Blood tests** ^**1**^	X		X	X^7^	X	X	X	X	X	X	X	X	X
**EDTA creatinine clearance**				X^2^									
**Fitness for surgery**	X												
**Imaging (RECIST v1.1)**	X				X			X				X	X
**Institutional SOC treatment**		Participants will receive either rRPLND or other institutional SOC treatment if not eligible/decline rPLND Treatment details will be collected on the Case Report Forms (CRF)		Participants to receive adjuvant chemotherapy if applicable									
**Surgical outcome & complications**			X	X	X	X							
**Adverse events**		AEs will be collected from the date of consent until 6 weeks post rRPLND or the end of treatment depending on the allocated treatment.^6^											
**Tumour sample**	X^3^	X											
**Research blood sample**	X		X		X^7^								X
**Patient reported outcomes** ^**4**^	X		X	X	X	X		X		X		X	X
**Disease, treatment, survival FU** ^**5**^						X	X	X	X	X	X	X	X

^1^
Serum tumour markers, urea and electrolytes, liver function tests and full blood count. Tests may be carried out up to ≤72 hours before the day of treatment.

^2^
To be carried out prior to adjuvant treatment only for participants who undergo chemotherapy.

^3^
Archival FFPE tumour sample from previous biopsy or orchidectomy.

^4^
Patient reported outcome information collected via questionnaires: EORTC QLQ‐TC26, EORTC QLQ‐C30, BMSFI and supplementary questions.

^5^
Disease, treatment and survival follow‐up information may be collected in clinic or via a telephone call with the participant.

^6^
For participants that are not eligible/decline rRPLND, AEs will be collected from the date of consent until 6 months post the end of treatment depending on the allocated treatment.

^7^

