Only for participants that receive adjuvant chemotherapy.

**TABLE 3 bco270057-tbl-0003:** Schedule of assessments carboplatin AUC10 cohort.

	Screening	Chemotherapy (cycle 1–3)	2 weeks	6 weeks	12 weeks	6 months	9 months	12 months	15 months	18 months	21 months	24 months	Disease recurrence
	<2 weeks prechemotherapy		± 2 weeks	± 1 week	± 2 weeks	± 2 weeks	± 2 weeks	± 4 weeks	± 4 weeks	± 4 weeks	± 4 weeks	± 4 weeks	+4 weeks
**Informed consent**	X												
**Demographic data & medical history**	X												
**Blood tests** ^**1**^	X	X	X		X	X	X	X	X	X	X	X	X
**EDTA creatinine clearance**	X												
**Imaging** *(RECIST v1.1)*	X		X					X				X	X
**Institutional SOC Treatment**		Participants will receive either Carboplatin AUC10 or other institutional SOC treatment if not eligible/decline Carboplatin AUC10. Treatment details will be collected on the CRF.											
**Adverse events**	AEs will be collected from the date of consent until 6 months post the end of treatment depending on the allocated treatment.												
**Tumour sample**	X^2^												
**Research blood sample**	X		X										X
**Patient reported outcomes** ^**3**^	X		X	X	X	X		X		X		X	X
**Disease, treatment and survival FU** ^**4**^						X	X	X	X	X	X	X	X

^1^
Serum tumour markers, urea and electrolytes, liver function tests and full blood count. Tests may be carried out up to ≤72 hours before the day of treatment. Test might be carried pre‐treatment for every cycle.

^2^
Archival FFPE tumour sample from previous biopsy or orchidectomy.

^3^
Patient reported outcome information collected via questionnaires: EORTC QLQ‐TC26, EORTC QLQ‐C30, BMSFI and supplementary questions.

^4^
Disease, treatment and survival follow‐up information may be collected in clinic or via a telephone call with the participant.

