### Methods of data collection

5.4

*Demographic data*: Age, sex, date of birth and race/ethnicity will be collected with participants' consent, along with a comprehensive medical history including previous conditions, surgeries, cancer history and detailed testicular cancer diagnosis.

*Blood samples*: Serum tumour markers (AFP, BhCG, LDH) will be taken at screening and analysed locally. Results will be recorded in CRF, with clinically significant treatment‐related abnormalities noted as AEs. For participants undergoing rRPLND, surgical outcomes will be recorded, including complications, hospital stay and recovery time, up to six months post‐surgery.

*Imaging*: Centres that perform rRPLND typically undertake a baseline PET scan prior to surgery to determine eligibility. Positron Emission Tomography (PET) is typically not used in centres treating participants with Carboplatin AUC10. PET is not mandated for this trial; however, if a baseline PET is undertaken as part of institutional SOC, the results will be collected. All tumour assessments will be performed using Computed Tomography (CT) scans following the schedule of assessments. If contrast CT is contraindicated, Magnetic Resonance Imaging (MRI) scans and non‐contrast CT scans may be used. RECIST v1.1 criteria will be used to assess participants response.

*Health‐related quality of life*: Will be assessed using standardised validated questionnaires (EORTC QLQ‐TC26, EORTC QLQ‐C30, BMSFI and additional bespoke enquires on anejaculation), self‐administered using paper‐based format by participants. Site staff will assist if needed and document reasons for any uncompleted questionnaires. Completed patient‐reported outcomes (PRO) questionnaires will be sent to the coordinating team, with originals kept in patient records.

*Adverse event*: Will be tracked from consent to six weeks post‐rRPLND and six months post‐chemotherapy. Unresolved AEs at study end will be followed up by the Investigator but without further recording in the CRF.

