### Adverse event reporting and harms

5.7

The Safety Reporting Instructions for the THERATEST trial outline the procedures for reporting and managing AEs and SAEs. An AE is defined as any unfavourable medical occurrence in a participant, regardless of its relationship to the research procedure. SAEs are more severe, meeting specific criteria such as being life‐threatening or requiring hospitalisation.

AEs are recorded from the time of informed consent until the safety visit and are tracked in the eCRF. Certain events, such as elective hospitalisations, are excluded from SAE reporting. SAEs must be reported to the THERATEST Coordinating Team within 24 hours using the THERATEST SAE Reporting Form. The form must be fully completed, including details like event severity, relatedness to the study and outcome. The coordinating team verifies the form's completeness and liaises with the site for any additional information. If an SAE is deemed both related to the study and unexpected, a non‐CTIMP safety report must be sent to the Research Ethics Committee (REC) within 15 days. Follow up reports are required as new information arises, ensuring thorough documentation and communication with the sponsor.

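### Adverse-event collection follows the allocated treatment and does not reopen at recurrence, so most toxicity of relapse treatment after rRPLND would go ungraded

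*Protocol article*

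**What the plan says.** The safety objective in section 3.2 of the protocol article is broad: "The study seeks to assess the safety and complications associated with all treatments". The AE window in the same section is narrow: "from the time of informed consent until 6 weeks post‐surgery or 6 months post‐chemotherapy".

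The window is described again in four places:

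- Table 2 (rRPLND cohort): "AEs will be collected from the date of consent until 6 weeks post rRPLND or the end of treatment depending on the allocated treatment". Its footnote 6 gives participants who do not have rRPLND 6 months from the end of treatment.
- Table 3 (Carboplatin AUC10 cohort): "AEs will be collected from the date of consent until 6 months post the end of treatment depending on the allocated treatment".
- Section 5.4: "Will be tracked from consent to six weeks post‐rRPLND and six months post‐chemotherapy".
- Section 5.7: "AEs are recorded from the time of informed consent until the safety visit and are tracked in the eCRF". Neither schedule table names a safety visit.

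Both tables have a Disease recurrence column. It is marked for blood tests, imaging, research blood, patient-reported outcomes and disease, treatment and survival follow-up. The AE row has no entry there. Section 5.1.1 adds "Information regarding anti‐cancer treatments will be collected for all participants throughout the follow‐up period", so treatment given for relapse is itself recorded.

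**The concern.** De-escalation accepts some extra relapse in exchange for less toxicity at the start. A fair safety account of a strategy therefore includes the toxicity of treating the relapses that follow it. As written, AE collection covers the first treatment and then stops. A participant who relapses later has the further treatment recorded, but not the type and grade of the harm it causes.

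The omission is not neutral if one group has both a shorter window and more relapses. By the figures in the Background that group is rRPLND, and the effect would be to make its safety record look better than it is. The article says that the study should give a later definitive trial prospective information on safety and complications. AEs that were never collected cannot be recovered by any analysis plan.

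**Working it through.** The article gives no sample size calculation, so there is no planned figure to reproduce. The check sets the AE windows against the schedule for finding relapse, then sizes the gap.

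**1. Window against schedule**

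| | rRPLND | Carboplatin AUC10 |
|---|---|---|
| AE window closes | 6 weeks after surgery | 6 months after end of treatment |
| Scheduled scans after treatment | 12 weeks, 12 and 24 months | 2 weeks, 12 and 24 months |
| Tumour markers inside the window | 2 weeks; 6 weeks only with adjuvant chemotherapy | 2 weeks, 12 weeks, 6 months |

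After rRPLND the earliest scan is at 12 − 2 = 10 weeks, using the visit allowance. No scheduled post-operative scan falls inside 6 weeks. After Carboplatin AUC10 one scan and three marker tests fall inside the window.

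**2. Cited relapse rates (Background)**

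- RPLND: 10% at up to 9 months; 100 − 81 = 19% at 2 years; 31% over a mean of 26 months.
- Carboplatin AUC10: 100 − 96.5 = 3.5% progression or death at 2 years.
- Standard of care (section 3.2 aim of above 95%): below 5% at 2 years.

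The source of the highest figure is described thus: "RPLND without adjuvant chemotherapy in stage IIA/B seminoma showed a 31% recurrence rate over a mean of 26 months follow‐up".

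**3. Share of relapses occurring inside the window**

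Assume a constant hazard. With S the relapse-free proportion at time T and w the window, the share is (1 − S^(w/T)) / (1 − S).

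- rRPLND, 19%: (1 − 0.81^(6/104.36)) / 0.19 = 0.063.
- rRPLND, 31%: (1 − 0.69^(6/113)) / 0.31 = 0.063.
- Carboplatin AUC10, 3.5%: (1 − 0.965^(26.09/104.36)) / 0.035 = 0.253.
- Standard of care, 5%: (1 − 0.95^(26.09/104.36)) / 0.05 = 0.255.

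About 94% of relapses after rRPLND, and about 75% after Carboplatin AUC10 or standard treatment, would occur after AE collection has closed. These shares concern when relapse occurs. Its treatment starts later, so even a relapse inside the window would have only part of its treatment covered.

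**4. Number of participants**

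Section 2.2 sets at least 5 per de-escalation group and at most 15 on standard treatment, out of 30. If 15 are de-escalated and 5 have Carboplatin AUC10, rRPLND has 15 − 5 = 10. The range 5 to 10 is an assumption, since fewer than 15 on standard treatment would allow more.

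| Group, rate | n | Expected relapses n × p | At least one, 1 − (1 − p)^n |
|---|---|---|---|
| rRPLND, 10% | 5 to 10 | 0.5 to 1.0 | 0.41 to 0.65 |
| rRPLND, 19% | 5 to 10 | 0.95 to 1.9 | 0.65 to 0.88 |
| rRPLND, 31% | 5 to 10 | 1.55 to 3.1 | 0.84 to 0.98 |
| Carboplatin AUC10, 3.5% | 5 to 10 | 0.18 to 0.35 | 0.16 to 0.30 |
| Standard of care, 5% | 15 | 0.75 | 0.54 |

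**The case against.** A reader might infer that collection closes before any relapse can be found, and that the safety result therefore favours de-escalation in general. The documents do not support this. After Carboplatin AUC10 a relapse could be found by the 2-week scan, by markers or clinically while AEs are still collected. That window is the same 6 months as for standard chemotherapy, and 3.5% lies within the standard-of-care aim. Equal windows and similar relapse give no differential omission.

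Nor is the 2-year burden of each strategy wholly unrecorded. Anti-cancer treatments are collected throughout follow-up. Patient-reported outcomes run to 24 months and are repeated at recurrence. Relapse counts in progression-free survival, and surgical complications are followed to 6 months.

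The RPLND rates also need care. The 31% is from surgery without adjuvant chemotherapy, whereas Table 1 lists adjuvant treatment as typical for node-positive disease. The Background also describes apparently low relapse when one adjuvant carboplatin cycle follows rRPLND. The rates are upper values wherever adjuvant treatment is given.

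Three further arguments carry less weight:

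- The objective's reference to all treatments may mean only the study treatments, so it does not by itself contradict the window. The window still omits relapse toxicity on either reading.
- The 6 months after chemotherapy in sections 3.2 and 5.4 could be read to include chemotherapy for relapse. The tables' tie to the allocated treatment points the other way, and sites could apply the rule differently.
- The full protocol and the separate safety reporting instructions are not shown and may contain a rule for relapse. However, the article states the window explicitly in several places, so this is more than detail lost in condensing.

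Finally, this is a 30-participant, non-randomised feasibility study with recruitment as its primary endpoint. A few participants cannot settle a toxicity comparison. That limits the seriousness of the gap but does not remove it.

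**Conclusion.** The point holds in a limited form. AE collection is anchored on the allocated treatment, and nothing in the article reopens it at recurrence. After rRPLND it closes at 6 weeks, before any scheduled post-operative scan. What is lost is the CTCAE type and grade of toxicity from treating most relapses; the treatments themselves and patient-reported outcomes are kept.

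A directional effect is shown only for rRPLND, which combines the shortest window with the highest cited relapse rates. About 1 to 3 participants would be affected, assuming 5 to 10 in that group and relapse of 19% to 31%. The 94% timing share rests on a constant hazard and on the 6-week reading of the window. Participants given adjuvant chemotherapy may fall under the longer 6-month rule, which the article leaves unclear. This is a worthwhile, inexpensive improvement to a secondary objective and does not threaten the primary endpoint.

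**What to change.** 1. Reconcile the AE windows in sections 3.2, 5.4 and 5.7 and in Tables 2 and 3. Define the safety visit, and state which window applies when adjuvant chemotherapy follows rRPLND.
2. State that AE and serious AE recording reopens at the start of any treatment for recurrence and runs to the 24-month visit at the latest.
3. Add AEs to the Disease recurrence column of both tables.
4. Report toxicity by initial strategy twice: for initial treatment only, and cumulatively to 24 months including treatment for relapse.

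This changes data collection and reporting only, with no change in sample size or length of follow-up. It needs a protocol amendment and reuse of the existing eCRF AE pages for a few participants. The downside is slightly more site data entry and possibly a less favourable safety figure for rRPLND.
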